### Sample Size

#### Overview

MRTs are often more statistically efficient than traditional randomized trial designs because they leverage both between-subject and within-subject contrasts of proximal outcomes. However, the efficiency gains of an MRT depend on the number of decision points contributed per participant. The current MRTs will include 2 decision points within a single visitor session on the MHA website. This design provides fewer within-person contrasts than high-frequency MRTs (eg, daily notification studies), as each participant can contribute at most 2 randomizations across the session. Consequently, statistical power in this study is primarily driven by the between-subject sample size rather than the repeated within-person contrasts. This structure reflects constraints of the intervention context. The current trial is a web-based, naturalistic engagement study that embeds randomizations within the existing ecosystem of a real-world DMH platform, where pull intervention delivery must align with the typical website navigation flow rather than repeated daily push notifications.

The minimum sample size was calculated for MRTs with binary proximal outcomes [36,45-47]. Calculations assumed 80% power, a 2-sided α of .05, and a treatment randomization probability of 0.80 for the primary pooled analysis (ie, probability of being assigned any HAPA-based engagement strategy vs control at a given decision point). An expected availability of 0.70 was used in the calculation. This reflects the expected availability averaged over time [46], including full availability at decision point 1 (as all eligible participants view the Screening Results Page) and a conservatively lower availability at decision point 2 (as preliminary analyses indicated that under standard conditions, most MHA visitors bounce after receiving their screening results, with fewer navigating to content pages). Participants who do not navigate to a Next Steps Content Page are not available for randomization at decision point 2. Under the assumption of a constant success probability under the null of 0.30 (a conservative estimate given that 63% of visitors leave the MHA website after viewing screening results) and a proximal treatment effect of 1.20 on the relative risk scale, an estimated 2300 participants will be required to detect a marginal causal excursion effect with 80% power. These assumptions reflect engagement patterns observed in prior analyses of MHA’s site use and account for the time-bounded, single-session nature of the intervention. Given the volume of visitors to MHA’s Online Screening Program, it is possible that the final sample size will exceed this minimum requirement. However, final enrollment numbers will ultimately reflect the naturalistic rate at which eligible visitors access MHA’s Online Screening Program throughout the duration of the study. Importantly, the study uses an iterative series of MRTs in which successive MRTs are conducted and engagement strategies are refined between iterations. Each MRT iteration requires approximately 2300 participants to detect an effect within the primary pooled analysis. To power secondary analyses comparing specific HAPA behavioral determinants against control or specific message or card against control, each MRT iteration will need a larger sample. These analyses will be interpreted as exploratory.

#### Recruitment

Given the real-world setting of this study and focus on naturalistic engagement as the primary outcome, no active recruitment or retention procedures will be implemented.

#### Intervention Assignment

##### Sequence Generation

As there will be no active recruitment for this trial, eligibility assessment will occur automatically following a visitor’s completion of the PHQ-9 depression screening and optional questions within MHA’s Online Screening Program (see *Eligibility Criteria* section).

Eligible participants will encounter 2 randomization decision points embedded within the usual flow of the Online Screening Program. The first decision point occurs on the Screening Results Page, where participants receive their PHQ-9 score, brief information about their score, and a set of 3 to 4 targeted Next Steps Content Pages. At this point, participants will be randomized with equal probability to either receive no engagement strategy (ie, standard Screening Results Page) or an engagement message targeting 1 of 4 HAPA behavioral determinants (ie, outcome expectancy, perceived risk, self-efficacy, and SGM-specific barriers to engagement). Here, engagement strategies are drawn from a bank of messages developed to operationalize each determinant.

The second decision point will occur when participants navigate to a targeted Next Steps Content Page from the Screening Results Page. At this point, participants will again be randomized with equal probability to either receive no engagement strategy (ie, standard Next Steps Content Pages) or an engagement card targeting 1 of the same 4 HAPA behavioral determinants. Here, engagement strategies are drawn from a bank of cards developed to operationalize each determinant.

Randomizations will be independent across decision points. Randomization probabilities will be fixed across participants and do not depend on prior randomizations, engagement outcomes, or participant characteristics.

##### Allocation Concealment Mechanism and Blinding

Participants will not be explicitly informed that engagement strategies are being experimentally manipulated due to the naturalistic design of the trial and the waiver of consent. Participants will experience engagement strategies as part of the MHA interface and will not be notified of their assigned condition, the existence of multiple conditions, or randomization schedules. Engagement strategies will not alter navigation options or restrict access to content.

##### Implementation

Randomization with equal allocation across conditions will be implemented at each decision point through MHA’s web infrastructure. The randomization logic was developed in collaboration with MHA’s research team and will undergo QA testing prior to the launch of each MRT iteration to ensure correct allocation probabilities and independence across decision points. Delivery of engagement strategies will occur passively within the existing website interface and does not require additional participant actions beyond normal site navigation.

### Data Analysis Plan

#### Primary Aim Analysis

Analyses will estimate the marginal causal excursion effects of delivering engagement strategies on proximal engagement with MHA content. Data will be analyzed using the weighted centered least squares estimator, which provides consistent estimates of causal excursion effects when including time-varying factors that may be influenced by prior intervention exposure [36,45,48]. Analyses will examine whether, on average, across decision points, engagement strategies (A*_t_*-D*_t_*) increase proximal engagement with targeted MHA content relative to the control (Z*_t_*). A log-linear model will be used, as the primary proximal outcome is binary (engaged vs not engaged with targeted content). For the primary analysis, all HAPA-based engagement strategies (A*_t_*-D*_t_*) will be pooled so that the estimated marginal causal excursion effect represents the average effect of delivering any engagement strategy compared with the control (Z*_t_*). Effects will be expressed as the log of a risk ratio (ie, the probability of engagement when an engagement strategy is delivered relative to the probability of engagement when the control is delivered at a decision point). To examine whether intervention effects differ across the 2 decision points, models will include an interaction between intervention assignment and a decision point indicator. Baseline characteristics (eg, sexual orientation, gender identity, age, baseline PHQ-9 score, and intentions for using MHA) and time-varying contextual factors (eg, number and type of pages visited prior to a decision point) will also be examined as potential moderators of proximal intervention effects by including interaction terms in the log-linear model. Models will control for race or ethnicity and income.

#### Secondary Aim Analysis

Secondary analyses will examine whether engagement strategies targeting distinct HAPA behavioral determinants differ in their relative effectiveness at increasing proximal engagement with targeted MHA content. Using the same weighted centered least squares estimation approach, models will compare the proximal effects of strategies targeting outcome expectancy (A*_t_*), risk perception (B*_t_*), self-efficacy (C*_t_*), and SGM-specific barriers to engagement (D*_t_*). These analyses will estimate marginal causal excursion effects for each strategy type. Additional analyses will examine whether variations of engagement strategies within the bank that target the same HAPA behavioral determinant differentially impact proximal engagement. These exploratory comparisons will be conducted by extending the primary regression models to include indicators for specific engagement strategy variations and estimating their relative causal excursion effects on proximal engagement outcomes. Exploratory analyses will also examine additional engagement outcomes (as described in the *Measures* section), including time spent on pages and the number of additional pages visited following exposure to intervention content.

#### Missing Data

Proximal outcomes at both decision points are defined using website event data and are expected to be largely complete. Missing proximal outcomes may occur due to both technical factors (eg, logging errors) and behavioral processes (eg, participants who disengage before a decision point are not available for randomization). Indicators required for eligibility assessment are expected to be complete, but some moderators and covariates may be missing as postscreening survey items are optional.

45
48

The primary analysis will use all available decision points with observed proximal outcomes (ie, complete-case analysis at each decision point), an approach consistent with recommendations for addressing missing data in MRTs [49]. If missing data are ≤10%, results will be interpreted with minimal concern for bias. If missingness exceeds this threshold, patterns of missing data will be summarized at each decision point and compared across experimental conditions and observed participant characteristics. Exploratory analyses will examine whether intervention effects differ depending on patterns of missingness.

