**Methods:**

Eligible participants will be MHA visitors who complete the Patient Health Questionnaire-9 depression screening test in English and indicate on an optional postscreening survey that they live in the United States, are aged ≥14 years, and identify as LGBTQ+ (lesbian, gay, bisexual, transgender, queer, and other SGM populations). Participants will be randomized at 2 decision points embedded within the MHA Online Screening Program. At each decision point, participants will be randomized with equal probability (0.2) to receive no engagement strategy or an engagement strategy targeting 1 of 4 Health Action Process Approach behavioral determinants, including outcome expectancy, risk perception, self-efficacy, or SGM-specific barriers to engagement. The primary outcome will be proximal engagement with MHA content, operationalized at decision point 1 as click-through to a targeted Next Steps Content Page and at decision point 2 as click-through to any additional MHA content page. The primary analysis will estimate the marginal causal excursion effect of delivering any engagement strategy compared with the control.

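### A pooled missingness of 10% or less cannot by itself justify minimal concern for bias; missingness should be compared by condition whatever the total

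*Protocol article*

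**What the plan says.** The Missing Data section of the Data Analysis Plan fixes three things.

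- Handling: "The primary analysis will use all available decision points with observed proximal outcomes (ie, complete-case analysis at each decision point".
- Interpretation at or below the threshold: "If missing data are ≤10%, results will be interpreted with minimal concern for bias".
- Action above it: "If missingness exceeds this threshold, patterns of missing data will be summarized at each decision point and compared across experimental conditions and observed participant characteristics".

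The section names logging errors as a technical source of missing outcomes. Its one behavioral example is visitors who leave before a decision point and so are never randomized there. It expects outcomes to be largely complete. A closing sentence on exploratory analyses asks whether intervention effects differ by missingness pattern; that is not a comparison of missingness between conditions.

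On allocation, the abstract's Methods say "At each decision point, participants will be randomized with equal probability (0.2) to receive no engagement strategy" or one of four strategies, and the sample size section uses "a treatment randomization probability of 0.80 for the primary pooled analysis". Control therefore holds 0.20 of randomizations.

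**The concern.** The rule settles the interpretation from one pooled number and omits the by-condition comparison in the range where it offers reassurance. A pooled total does not determine whether a complete-case risk ratio is biased. Loss that is random within each condition leaves the ratio unbiased however large it is, while loss that differs by condition and is related to clicking can bias it when small. With a 4:1 split between strategy and control, the total is dominated by the strategy arm and says little about control.

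At stake is the label put on the primary result. Followed literally, a risk ratio could be reported as being of minimal concern without anyone having tabulated missing outcomes for control against strategy. The complete-case analysis itself is not contested, only the presumption attached to it.

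**Working it through.** **Inputs** (Sample Size, Overview): control click probability 0.30 ("Under the assumption of a constant success probability under the null of 0.30"), planned RR 1.20 and hence a strategy probability of 0.36, strategy share 0.80, control share 0.20, average availability 0.70 over two decision points (1.4 randomizations per participant), N = 2300.

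**1. The plan's own figure.** With a log risk ratio, the variance factor per participant is [(0.64/0.36)/0.80 + (0.70/0.30)/0.20]/1.4 = (2.222 + 11.667)/1.4 = 9.921. Then N = (1.960 + 0.842)² × 9.921/(ln 1.20)² ≈ 2342. The MRT formula for binary outcomes with an F reference gives 2345. Both are within about 2% of 2300, so the inputs are read as the plan intends. At N = 2300 there are 2300 × 1.4 = 3220 randomizations: 644 control and 2576 strategy.

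**2. What a 10% total can contain.** If all loss were in control, 0.10/0.20 = 50% of control outcomes could be missing at a 10% total.

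**3. Worst-case bounds.** Only one arm and one outcome are lost; x is the share of that arm's randomizations.

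| Scenario | Equation | Share of arm | Share of all |
|---|---|---|---|
| Null read as RR 1.20, control clickers lost | (0.30 − x)/(1 − x) = 0.25 | 6.7% | 1.3% |
| Null read as RR 1.20, strategy non-clickers lost | 0.30/(1 − x) = 0.36 | 16.7% | 13.3% |
| RR 1.20 read as 1.00, strategy clickers lost | (0.36 − x)/(1 − x) = 0.30 | 8.6% | 6.9% |
| RR 1.20 read as 1.00, control non-clickers lost | 0.30/(1 − x) = 0.36 | 16.7% | 3.3% |

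These patterns are extreme. The first means losing 0.067/0.30 = 22% of control clickers and nobody else; the third means losing 0.086/0.36 = 24% of strategy clickers and nobody else. The second exceeds 10% and would trigger the plan's own comparison.

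**4. Loss that acts alike in both arms.** Let 10% of all outcomes be lost, all clickers or all non-clickers, at the same outcome-specific rate in each arm. A null stays at RR 1.00, and RR 1.20 is read as 1.22 (clickers lost) or 1.19 (non-clickers lost).

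**5. What a bounds analysis would show.** With a share m missing in each arm and observed rates q0 (control) and q1 (strategy), the limits are q1(1 − m)/[q0(1 − m) + m] and [q1(1 − m) + m]/[q0(1 − m)]. For an observed RR of 1.20, m = 0.10 gives 0.324/0.370 = 0.88 to 0.424/0.270 = 1.57; m = 0.05 gives 0.342/0.335 = 1.02 to 0.392/0.285 = 1.38. The direction of an observed RR of 1.20 survives the extreme bounds at 5% missing in each arm but not at 10%.

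**6. The denominator.** Average availability of 0.70 with full availability at decision point 1 implies 0.40 at decision point 2, so 30% of person-by-decision-point slots are unavailable. If unavailability counted as missing, the 10% threshold would be exceeded by design and the comparison would always run. If only outcomes missing after randomization count, it may never run. The section does not say which is meant.

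**The case against.** The strongest reply is that few outcomes can be missing at all. The Primary Engagement Outcomes section scores a participant who does not navigate as *no*, and engagement is read from server logs. An unlogged click would usually stay in the denominator as a false *no* and would not be dropped. That stands. It lowers the risk from missing outcomes, and it also means the threshold does not count that error: miscoding 0.05/0.30 = 16.7% of control clicks, 1.0% of all randomizations, would also turn a null into RR 1.20. The sensitivity run proposed here would not detect this either; the QA monitoring of outcome capture described under Results is the safeguard for it.

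Three further points stand. The only behavioral source the plan names arises before randomization, so it gives no evidence of outcome-related loss afterwards. No mechanism is given for excess loss in control; added messages or cards could at most suggest faults in the strategy arm, where creating RR 1.20 from a null needs 13.3% overall. And QA before and during each MRT is aimed at large arm-specific faults.

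A reader might infer that losses well under 10% are likely to create or erase the result, or that the 10% tolerance is too wide because it exceeds the 6-point planned effect. The documents support neither. They give no missingness rate by condition, and a missingness proportion and a risk difference are different quantities.

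The reply does not rescue the rule. QA does not alter the stated interpretation, and an expectation of near-complete data is no reason to omit the table that would confirm it.

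**Conclusion.** The presumption is unsound as written and should be replaced; the practical risk is modest. The figures of 1.3% and 6.9% of all randomizations are worst-case bounds. They rest on the plan's 0.30 control rate, RR 1.20 and 0.80 strategy share, and on loss confined to one arm and to clickers, which nothing in the protocol documents. They show only that a total below 10% cannot rule out material bias. They do not show that the primary risk ratio will be biased or that N needs to change. The ambiguity over whether unavailability at decision point 2 counts toward the 10% is a second reason to rewrite the sentence.

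**What to change.** - Delete the sentence that equates a total of 10% or less with minimal concern for bias.
- Define missingness as a proximal outcome missing after an actual randomization, excluding unavailability at decision point 2.
- Report and compare it for control versus strategy at each decision point, whatever the total.
- Add one sensitivity analysis of the pooled risk ratio: missing outcomes all scored as *no*, then at the arm-specific bounds (strategy *no* with control *yes*, and the reverse). Base the statement about bias on whether the conclusion survives.

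The cost is a few lines of text, one small table and one additional sensitivity analysis of the primary model per MRT iteration. No new data and no change to sample size or design are needed. The downside is slightly more reporting.

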### Ethical Considerations

#### Institutional Review Board Approval

This trial protocol was reviewed by the single institutional review board (sIRB) at the University of Washington and approved on December 3, 2025 (STUDY00017726). The QT-Digital Mental Health Engagement study is considered a multisite clinical trial, as MHA is involved in the following research activities: (1) performing research procedures; (2) administering study interventions; and (3) obtaining, using, or analyzing identifiable data. The external Data Safety and Monitoring Board was provided with protocol documents prior to the initiation of data collection and did not identify any foreseeable risks. Any major protocol modifications will be reviewed by the sIRB and the Data Safety and Monitoring Board and updated on the ClinicalTrials.gov registration.

#### Waiver of Consent

A waiver of consent was approved by the sIRB to facilitate the examination of naturalistic engagement. This waiver was supported by (1) MHA’s privacy policy, which informs visitors who use the site’s screening tools that deidentified data may be shared with universities for research and quality improvement purposes (Multimedia Appendix 1); and (2) the study’s minimal risk classification, as participants can continue to access MHA’s content across all conditions. In this study, formal consent procedures may also prevent naturalistic engagement. Prior research has found that participants recruited explicitly for DMH research engage differently than users who access DMH and are not identified as research participants [50]. Although participants will be randomized to different engagement strategies, these strategies introduce very minimal risk and are intended to optimize engagement with MHA’s available DMH resources.

#### Adolescent Participants

Along with the overall waiver of consent, a waiver of parental consent was approved for participants aged 14 to 17 years, as the protocol was designed for a subject population (here, SGM adolescents seeking readily available DMH resources via MHA’s platform) for which parental permission is not a reasonable requirement to protect this study subsample (45 CFR 46.408(c)). Generally, adolescents represent approximately 59% of MHA’s SGM visitors. In alignment, as of April 13, 2026, 52% (2004/3878) of study participants were SGM visitors aged 14 to 17 years. Including this user population is critical to understanding and optimizing the engagement behaviors of MHA’s SGM visitors, generally, and for this priority subpopulation. Adolescent-parental relational and communication issues are often cited as the main barriers to mental health care for SGM adolescents [51]. Besides disrupting natural engagement, requiring parental consent may cause safety concerns for those not ready to disclose their sexual or gender identity [52-54] or for those seeking DMH services due to relational concerns with their parents. The lower cutoff age of 14 years was chosen, as these adolescents represent high school–aged youth whom past research shows have similar health literacy as adults [55] and sufficient maturity and rational decision-making to self-consent to health and mental health care [56].

#### Risk Mitigation

MRT participants will be subject to minimal levels of risk, no greater than if they were to use the MHA platform without enrollment in this study. Participants reached and will engage with the MHA platform and Online Screening Program of their own volition. Although the study outcome is engagement, it is expected that most participants will have mental health symptoms or diagnoses. All MHA visitors have access to contact information for “warmlines” for each of the 50 states and phone and text crisis lines (eg, suicide and interpersonal violence), including those tailored to SGM populations. MHA visitors displaying any heightened level of risk for suicide (eg, anyone who responds “several days,” “more than half the days,” or “nearly every day” on the PHQ-9) are immediately prompted with the message “If you need immediate help, you can reach the Suicide & Crisis Lifeline by calling or texting 988 or using the chat box at 988lifeline.org. You can also text “MHA to 741-741 to reach the CrisisText Line. Warmlines (embedded link to warmline resources) are an excellent place for non-crisis support.” These mechanisms remain in place for study participants.

